### Outcome Measures

At enrollment, participants will sign a medical release of information form allowing the research team to measure data retrospectively from the participant’s medical records. To collect the self-report questionnaires for the enrollment and postpartum assessments, each participant will use a unique, secure link to complete the electronic questionnaires in REDCap at baseline after informed consent is signed and at 6 to 12 weeks post partum based on the participant’s due date. Reminders from the research team will be sent to participants using various forms of contact (phone and email) to complete the questionnaires as needed.

The following outcome measures will be used to examine the feasibility and acceptability of the PARITY intervention:

Feasibility will be assessed through enrollment, attrition, adherence to the intervention, and data collection.Enrollment rate: enrollment will be measured by the percentage of eligible individuals who agree to participate in the trial.Attrition rate: attrition will be measured by the percentage of eligible individuals who complete the study.Adherence to the intervention: adherence to the intervention will be measured using the Intervention Fidelity Checklist, where the doula interventionist will track when contact is made with participants and the number of doula sessions completed. Engagement with the platform will be tracked through clicks and the time spent on the platform.Data collection: data collection feasibility will be measured through study personnel’s sense of ease of use, time required, and missing data.Acceptability of and experiences with the intervention will be assessed using in-depth qualitative information gathered through interviews with intervention participants at 6 to 12 weeks post partum. Interviews will solicit (1) the usefulness of the intervention, (2) ideas to improve the intervention, (3) satisfaction with the intervention, and (4) the utility of innovative technology to deliver the intervention. The qualitative interviews will be audio recorded and transcribed verbatim.

The following outcome measures will be used to examine the preliminary efficacy of the PARITY intervention:

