### Sample Size Calculation for Future Full-Scale RCT

A sample size of 25 participants per group is sufficient to measure the proportional outcomes of recruitment efficiency and attrition for each group separately with an SE ≤0.10, assuming no attrition and worst-case variability (0.25) in each group. Past research suggests that attrition of up to 20% is acceptable and limits bias [26,27]. If there is up to 20% attrition in each group, the SE for each proportional outcome will be ≤0.12.

On the basis of Welch 2-sample 2-tailed *t* test, a minimum sample size of 25 participants per group provides 80% power to measure a difference in mean blood pressure and gestational weight change between the intervention and control groups of 0.81 multiplied by the SD, using a significance level of .05 [25]. If there is up to 20% attrition in each group, a difference of 0.91 multiplied by the SD is detectable with 80% power using a significance level of.05 [25]. We will recruit at least 5 additional participants per group, planning for screen failures or participant withdrawals.

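### The attrition rate is defined as completion among eligible people, contradicting the protocol's own use of attrition as loss within each randomized group

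*Protocol article*

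**What the plan says.** Outcome Measures names four feasibility components: "Feasibility will be assessed through enrollment, attrition, adherence to the intervention, and data collection". It then gives a rule for each. For the first, "enrollment will be measured by the percentage of eligible individuals who agree to participate in the trial". For the second, "attrition will be measured by the percentage of eligible individuals who complete the study".

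The section Sample Size Calculation for Future Full-Scale RCT also uses attrition. It calls 25 participants per group "sufficient to measure the proportional outcomes of recruitment efficiency and attrition for each group separately with an SE ≤0.10"; that figure takes the variance at its largest value, 0.25, and supposes that nobody is lost. It adds that "Past research suggests that attrition of up to 20% is acceptable and limits bias", that "If there is up to 20% attrition in each group, the SE for each proportional outcome will be ≤0.12", and that "If there is up to 20% attrition in each group, a difference of 0.91 multiplied by the SD is detectable with 80% power".

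Objectives lists retention among the things the pilot will inform, and Outcomes lists it among the aspects to be monitored. Neither section gives a formula for it.

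**The concern.** The rule under Outcome Measures has two faults.

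- **Direction.** The numerator is people who complete. Attrition is the share who do not, so a trial that loses nobody would report its highest possible attrition.
- **Denominator.** The enrollment sentence just before it uses the same eligible individuals as the base from which people agree to take part. They are therefore the pool before consent. People who were eligible but declined count against the figure, which mixes refusal with loss after randomization.

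Feasibility is the first objective, and attrition is one of its four named measures. Applied literally, the rule gives a number that is not attrition, cannot be set beside the 20% mentioned in the sample size section, and cannot show whether loss differs between arms.

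**Working it through.** **Inputs.** 60 randomized 1:1 (Abstract and Study Design); 25 per group, variance 0.25 and attrition up to 20% (sample size section). The article gives no enrollment rate, so 40% to 100% is assumed. For simplicity everyone who agrees is taken to be randomized.

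**1. What attrition means in the sample size section.**
- Without attrition: SE = sqrt(0.25/25) = 0.100, matching the stated limit of 0.10.
- With 20% attrition: 25 × 0.80 = 20 per group; SE = sqrt(0.25/20) = 0.112, within the stated 0.12.
- Two-sided two-sample t test at .05: power is 80.1% for 0.81 SD with 25 per group, and 80.1% for 0.91 SD with 20 per group.

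The figures reproduce, and they do so with attrition as the share of a randomized group that is lost (25 falling to 20).

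**2. What the rule under Outcome Measures computes.** Let E be eligible, R randomized and C completing.
- As written: C/E = (R/E) × (C/R) = enrollment rate × retention.
- Usual attrition: (R − C)/R.

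**3. Numbers for R = 60.**

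| Completing | Attrition, (60 − C)/60 | As written, enrollment 100% (E = 60) | 80% (E = 75) | 60% (E = 100) | 50% (E = 120) | 40% (E = 150) |
|---|---|---|---|---|---|---|
| 60 | 0% | 100% | 80% | 60% | 50% | 40% |
| 48 | 20% | 80% | 64% | 48% | 40% | 32% |
| 36 | 40% | 60% | 48% | 36% | 30% | 24% |

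In each enrollment column the figure falls as true attrition rises. That reversal does not depend on the assumed enrollment rate; the size of the discrepancy does.

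**4. Does taking the complement repair it?** No, unless everyone eligible enrolls. With E = 100 and C = 48, 1 − 48/100 = 52%, not 20%. With no loss at all, 1 − 60/100 = 40%, not 0%. The decliners are being counted as lost.

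**5. Can it be given by arm?** No. An eligible person who declined was never allocated, so E has no value within an arm. The sample size section nevertheless plans a measure for each group.

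**The case against.** The strongest reply is that this is a drafting slip that carried the enrollment wording into the next sentence. Elsewhere the article uses attrition and retention in the normal way. Counts of randomized and completing participants will exist by arm whatever this sentence says, so correct attrition can be computed at reporting. Recruitment is by self-referral, so eligible decliners may be few. In that case the figure is close to plain retention, and most readers would see that 80% means completion. The by-group phrase also covers recruitment efficiency, which cannot be split by arm either, so that sentence may itself be loose.

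Much of this stands, and it limits the consequences. It does not remove the contradiction. The rule is stated explicitly, no other text corrects it, and a reader who guesses the inversion still cannot tell whether the intended base is consented, randomized or eligible people. The sample size arithmetic shows the intended sense of attrition without relying on the by-group phrase.

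Three stronger readings are tempting, and the article does not support them:
- **That the larger trial would be mis-sized.** Nothing says this ratio feeds the next trial's sample size, and the sample size section reasons from loss within groups.
- **That the reported result is bound to be wrong.** It is wrong only if the sentence is followed literally.
- **That 20% is a feasibility threshold.** It is a cited planning allowance; the article attaches no progression criterion to attrition.

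**Conclusion.** The definition is wrong as written and contradicts the sample size section. Applied literally, it misreports one of four named feasibility outcomes. With 48 of 60 completing it gives 80% instead of 20% in the case most favourable to its denominator, where everyone eligible enrolls. Over assumed enrollment of 80% down to 40% it gives 64% down to 32%. Those lower values are illustrations only. The reversed direction and the impossibility of reporting by arm need no assumption about enrollment.

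The reach is limited. The efficacy analyses, the missing-data plan, and the stated standard errors and detectable differences do not use this definition and are unaffected.

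**What to change.** Replace the attrition sentence under Outcome Measures with a definition such as: the percentage of randomized participants who do not complete the 6 to 12 week postpartum follow-up, reported overall and by arm. Keep eligible individuals as the denominator of the enrollment rate only. The 20% in the sample size section may be cited for context, but should not be presented as a progression criterion unless the sponsor decides to set one.

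The cost is one sentence. No new data, extra visits or change to the sample size are needed. It is best settled before results are reported, so that the denominator is not chosen after the counts are known.

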Maternal blood pressure (primary) at 20 weeks, 36 weeks, birth, and 6 weeks post partum will be measured retrospectively from the medical record at 12 weeks post partum. The data will be analyzed as a continuous variable using the participant’s blood pressure (systolic and diastolic) as well as categorically with the blood pressure classifications of hypertension (>140/90) and severe hypertension (>160/110).Gestational weight gain (secondary), or the amount of weight gained in pounds at 20 weeks, birth, and 6 weeks post partum, will be measured retrospectively from the medical record at 12 weeks post partum.Cesarean birth (secondary) will be assessed from the delivery modality (vaginal, cesarean, or assisted vaginal delivery), measured retrospectively from the medical record at 12 weeks post partum.Perinatal outcomes (exploratory) from birth will be measured retrospectively at 12 weeks post partum via the maternal medical record. The perinatal outcomes that will be measured include preterm delivery; gestational diabetes; birth weight; gestational age at delivery; anesthesia used during labor; labor length; delivery provider type (obstetric physician, family physician, resident physician, or certified nurse midwife); and intrapartum medical diagnoses according to theInternational Classification of Diseases, 10th Revision[34], including hypertensive disorders of pregnancy, intrapartum fever, and postpartum hemorrhage. In addition, the Appearance, Pulse, Grimace response, Activity, and Respiration score of the newborn at birth will be measured as a way to summarize the health of the baby [35].

The following outcome measures will be used to investigate changes to wellness behavioral outcomes and empowered strengths:

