
### Data Analysis

Participants will be described using standard summary statistics and distribution plots of measured variables at each point in time. We will estimate the standardized magnitude of each baseline difference and the correlation between each baseline variable and each outcome of interest in the interim and primary end point of early participants to objectively determine baseline variables that will be needed to estimate the unbiased effect of PARITY on each outcome. A shared random component generalized linear mixed model (GLMM) will be used to simultaneously describe and compare the effects of PARITY on clinical outcomes, wellness-related behavioral outcomes, and empowered strength outcomes over the measurement periods [49]. A shared random component model will account for the correlation within participants on any 1 measure and the correlation between measures on the same participant at the same time point. The effect of time will be treated as a fixed effect. The time-by-group interaction will be tested; if the interaction *P* value is >.10, it will be dropped from the model. Baseline nutrition, physical activity, and sleep measures will be used as covariates to control for potential differences in the groups and to avoid detecting spurious time-by-treatment interactions due to the random assignment of participants to groups. Demographic or clinical characteristics exhibiting differences between groups at baseline will be investigated as potential covariates in the models. For significant effects, preplanned post hoc contrasts will be computed, and *P* values will be adjusted using the Holm method to maintain comparison-wise error at or <.05 [50]. Unless otherwise specified, the significance level for all tests will be.05.

Missing outcome data caused by loss of follow-up are possibly related to the participant’s unobserved outcome measures (nonignorable missingness). The GLMM provides unbiased estimates under missing completely at random and missing at random mechanisms. The data will be reanalyzed using a pattern-mixture model (PMM) to allow for different coefficient changes based on dropout patterns [51]. GLMM and PMM marginal treatment effects will be compared. If the marginal treatment effects differ by >10%, the missingness mechanism will be assumed not at random, and the PMM model marginal estimates will be used to draw conclusions.

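### The primary blood pressure outcome is four variables over three follow-up times with none designated, and no adjustment across the four is stated, so the false-positive rate on the primary exceeds the planned .05

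*Protocol article*

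**What the plan says.** - **Outcome.** Outcome Measures states: "Maternal blood pressure (primary) at 20 weeks, 36 weeks, birth, and 6 weeks post partum will be measured retrospectively". It is to be analysed as "blood pressure (systolic and diastolic) as well as categorically with the blood pressure classifications of hypertension (>140/90) and severe hypertension (>160/110". That makes four variables. The 20-week value is the starting point, which leaves three follow-up times. None of the variables or times is given priority.
- **Model.** Data Analysis states: "A shared random component generalized linear mixed model (GLMM) will be used to simultaneously describe and compare the effects of PARITY on clinical outcomes", and extends the same model to the behavioural and strengths outcomes. The time-by-group interaction is tested and dropped when its P value is above .10.
- **Level.** "Unless otherwise specified, the significance level for all tests will be.05".
- **Contrasts.** "For significant effects, preplanned post hoc contrasts will be computed", and their P "values will be adjusted using the Holm method to maintain comparison-wise error at or <.05". The Methods part of the Abstract describes the Holm goal in the same way. Neither place says which contrasts form the Holm set.
- **Sample size.** The sample size section states that "a minimum sample size of 25 participants per group provides 80% power to measure a difference in mean blood pressure" (and gestational weight change) of 0.81 SD, or 0.91 SD after 20% attrition, from a two-tailed Welch t test at .05. Study Design also claims 80% power at a .05 level.

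**The concern.** A .05 error rate and 80% power describe one pre-specified comparison. The text offers several routes to a significant primary result: an interaction or a group effect, on any of four variables. Holm enters only after one of these is already significant, and no adjustment between the four variables is stated. The sample size section does not say which blood pressure variable or time its single comparison refers to, so a reader of the results could not tell which one the .05 belongs to.

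The Objectives hypothesise that blood pressure will improve and aim to estimate an effect size, and the results are meant to inform a larger trial. If the most favourable of several blood pressure results were read as the primary finding, the evidence would look stronger than it is and the effect size would tend to be too large.

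The Holm wording adds to the confusion. A comparison-wise rate is what each unadjusted test already has. Holm controls the family-wise rate within a stated set, so its stated purpose is misnamed and its set is missing.

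**Working it through.** **1. The plan's own figures.** Inputs: Welch two-tailed t test, .05, 80% power, equal arms (sample size section). From the noncentral t with 2n − 2 degrees of freedom and noncentrality d√(n/2):
- n = 25 per group: detectable d = 0.809 SD; power at 0.81 SD is 80.1%.
- n = 20 per group: detectable d = 0.909 SD; power at 0.91 SD is 80.1%.

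Both stated values reproduce, for one comparison at .05. The document gives no family-wise error rate, so there is none to reproduce.

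**2. Reference values if the tests were independent.**
- One test on each of four variables: 1 − 0.95⁴ = 18.5%.
- Interaction first, then the group effect if the interaction P exceeds .10: 0.05 + 0.90 × 0.05 = 9.5% for one variable, and 1 − 0.905⁴ = 32.9% for four.

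These overstate the rate, because systolic pressure, diastolic pressure and categories cut from them are correlated.

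**3. Null simulation with correlation.** There were 10,000 trials per scenario with 25 per group. The inputs below are assumptions, not in the document: systolic-diastolic correlation 0.5 to 0.8; between-time correlation 0.3 to 0.7; means 118/73 or 128/80 mmHg; SDs 13 and 9.5 mmHg; a category is met if either limit is exceeded. For the readings that use the interaction step, the GLMM was replaced, variable by variable, by a repeated-measures group-by-time F test and a t test on the mean over times.

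| What counts as a positive primary result | Chance of at least one under no effect |
|---|---|
| One test per variable, four variables | about 8-13% |
| A significant group effect with the interaction dropped, or a significant interaction confirmed by a contrast Holm-adjusted over three times within that variable | about 11-15% |
| Any significant interaction or group effect, four variables | about 20-24% |
| The same, systolic and diastolic only | about 14-17% |
| The same, one variable | about 9-10% |

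**4. What the remedies give.** One named variable with one named test keeps 5%. Holm over four variable-level tests gives 2-3%, and Holm over all twelve variable-by-time tests also gives 2-3%. Naming a variable is not enough: the last row of the table shows that the interaction pre-test alone takes one variable to 9-10%, so the contrast must be named as well.

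**The case against.** **The plan does not run a separate test at each time.** This stands. Four variables at three times suggest twelve tests at .05, and a reader might infer a rate of 1 − 0.95¹² = 46%, or 17-32% with correlated data. The document does not support that reading. It fits one model over the measurement periods, and contrasts come only after a significant effect and are Holm-adjusted. Repetition over time is therefore partly covered. The gap lies in the model-level tests and between the variables.

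**The joint model deals with it.** This does not stand. The shared random component accounts for correlation within participants and between measures. It does not change the level of any test, and no single overall test of blood pressure is stated.

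**Holm works whatever it is called.** True: the wrong label does not turn Holm into an unadjusted procedure. The set it covers could be left to an analysis plan that is not shown. But the protocol itself fixes the .05 default, places Holm after a significant effect and states the wrong goal for it.

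**A primary is implied.** The continuous analysis is listed first and the sample size refers to mean blood pressure. This points away from the two categories, but it leaves systolic against diastolic, and the time or contrast, open.

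**It is a pilot.** Feasibility and acceptability come first, efficacy is called preliminary, and nothing makes the larger trial depend on a significant blood pressure result. This stands and lowers the severity. It does not remove the mismatch with the stated .05 and 80% power.

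**Conclusion.** The point holds. The primary blood pressure outcome has no designated variable, time or contrast, no adjustment across its four variables is stated, and the Holm family is undefined and its goal misnamed. The chance of at least one false-positive primary result is above the .05 used for the sample size on every reading examined that lacks such an adjustment.

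The size is roughly 8-24% under the stated model. The lower end counts one test per variable, and the upper end counts any significant interaction or group effect. A reader might take 20-24% as the rate the plan produces. That is only the top of the range, and all the simulated figures rest on correlations, SDs and blood pressure levels that the document does not give, and on a simplified stand-in for the GLMM.

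The detectable differences of 0.81 and 0.91 SD are correct for a single comparison. Sizing on a t test while analysing with a mixed model is ordinary practice and is not criticised here. The severity is modest.

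**What to change.** 1. In Outcome Measures and Data Analysis, name one blood pressure variable and one post-randomisation time or model contrast as primary, for example the GLMM treatment contrast for mean systolic pressure. This matches the single comparison in the sample size section. A contrast over the follow-up period keeps the longitudinal design and does not depend on every participant having a 36-week value, which births before 36 weeks would lack.
2. Report diastolic pressure, the two hypertension categories and the other times as secondary, as estimates with 95% CIs.
3. Alternatively, if all four variables are to stay primary, define one Holm family across all primary blood pressure tests, including the model-level ones.
4. In the Abstract and in Data Analysis, replace comparison-wise with family-wise and state the set of contrasts that Holm covers.

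The cost is wording only, with no new data and no change in sample size. The downside is that fewer results can be called primary. With the Holm family, each test also has less power than the single comparison in the sample size section.

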### Objectives

The overall purpose of this PARITY program is to reinforce protective assets through empowering messaging, promote wellness behaviors, and support Black birthing persons. This pilot trial will provide information on the feasibility, acceptability, and preliminary efficacy of the PARITY intervention among Black pregnant women as well as provide critical information on study design, retention, effect sizes, and outcomes assessment.

The objectives of this study are to (1) explore the feasibility and acceptability of the PARITY intervention; (2) investigate the preliminary efficacy of the PARITY intervention on changes to maternal blood pressure (primary), gestational weight gain, and cesarean birth (secondary) and estimate the effect size of the intervention relative to the control group; and (3) investigate changes to wellness behavioral outcomes (nutrition, physical activity, sleep, and health care adherence) and empowered strengths (self-efficacy, social support, motivation, resilience, problem-solving, and self-regulation) in PARITY intervention participants. With the combination of information, guidance, and support toward leveraging their innate strengths into actionable wellness, we hypothesize that the PARITY program will improve maternal blood pressure, gestational weight gain, and cesarean birth rate in the intervention group compared with the information-only control group. Further, we expect emphasizing individual strengths and building from them while navigating pregnancy-related health care will improve wellness behaviors and empowered strength variables such as adherence to medical care, including appointment adherence.

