### Study Population

Participants will be included in the study based on the following criteria: (1) self-identify as being of Black race, (2) pregnant with gestational age 20 to 28 weeks at enrollment, (3) ability to read and write in the English language, (4) planning to give birth in a health care facility and receive obstetrical care with a health care record, (5) reside within 20 minutes of the identified metropolitan area, (6) 19 to 51 years of age, and (7) own a smartphone with internet access. Participants will be excluded from the study for the following reasons: (1) current involvement in another intervention study, (2) planned pregnancy termination, or (3) inability to provide informed consent.

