##### Nutrition

PARITY includes information on nutrition during pregnancy and beyond. Nutritional advice will focus on eating foods in unprocessed forms (eg, fruits, vegetables, and lean meat), preparing food instead of purchasing fast food, mindfulness in eating, and water consumption. These nutritional guidelines are consistent with healthy weight gain and multiple nutritional benefits without prescribing standards that may require excessive financial resources or exclude foods that may be culturally important to participants.

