### Outcomes

The feasibility of a full trial will be monitored throughout the study (eg, the randomization, recruitment, and retention of participants; data collection; and adherence). Additional data will be collected only on intervention participants. These include data on engagement with the PARITY intervention based on the number of hyperlinks clicked, time engaged in the content, and the number of doula sessions completed throughout the 12 weeks. A total of 10 to 15 intervention participants will be asked to complete a qualitative interview to discuss their experiences with the intervention and the acceptability of the technology component, doula component, and strength messaging component at 12 weeks post partum.

Clinical maternal outcomes (maternal blood pressure, gestational weight gain, delivery modality, and exploratory perinatal outcomes) will be measured at 20 weeks, 36 weeks, birth, and 6 weeks post partum and will be collected from the medical record. At baseline (20-28 weeks’ gestation), demographics, discrimination, and neighborhood variables will be assessed using self-report questionnaires administered via REDCap (Research Electronic Data Capture; version 14.3.11) [30,31]. At baseline and 6 to 12 weeks post partum, wellness-related behavior outcomes (nutritional intake, physical activity, and sleep quality) and empowered strengths (self-efficacy, social support, problem-solving, motivation, resilience, and self-regulation) will be measured using web-based self-report questionnaires in REDCap. In addition, health care adherence (the number of prenatal appointments) will be evaluated retrospectively using medical records.

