### Participant Allocation

Randomization allocation will be guided by the National Cancer Institute Clinical Trial Randomization Tool [32]. This tool generates an allocation scheme using the asymptotic maximal procedure. The following parameter inputs were used in the tool: trial size=60, maximum-tolerated imbalance=3; and arms (ratio 1:1). The output of this randomization allocation tool provides a schedule of randomization.

After signing the informed consent and release of medical record forms, participants will be emailed a secure link to complete the baseline enrollment surveys electronically in REDCap. In addition, each participant will be given the Healthy Pregnancy handout [33], Community Resources handout, and Birth Doula handout, in addition to the standard consent documents. Participants will be randomized according to the randomization schedule based on when they complete the enrollment surveys. Once a participant completes the enrollment surveys, the research coordinator will inform the participant of their group assignment and explain the procedures related to the assigned group.

Individuals randomized to the information control group will be dismissed and informed that they will be contacted by study personnel 6 to 12 weeks post partum to complete the follow-up assessments. Individuals randomized to the intervention group will be contacted by the doula interventionist to schedule their first doula session and be onboarded to the PARITY platform. The interventionist will explain that the participant will receive 3 additional sessions (4 in total) with the doula interventionist in addition to the mobile technology platform where communication can occur with the doula.

During the sessions, the doula interventionist will use the Doula Sessions Manual, which contains a script for each visit. The doula interventionist will track when contact is made with the participant on a form called the Intervention Fidelity Checklist. To ensure the fidelity of the intervention, the doula interventionist’s adherence to the intervention protocol will be measured through an audit of the dates and missed visits on the Intervention Fidelity Checklist and monthly review meetings.

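### Gestational weight gain counts a 20-week value fixed at or before randomisation and a postpartum value as outcome times, so the model can average the group effect over a time the program cannot affect

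*Protocol article*

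**What the plan says.** Outcome Measures defines the secondary outcome as "the amount of weight gained in pounds at 20 weeks, birth, and 6 weeks post partum", taken retrospectively from the medical record. The general Outcomes section says that the clinical outcomes as a group "will be measured at 20 weeks, 36 weeks, birth, and 6 weeks post partum and will be collected from the medical record"; that list includes a 36-week time which the weight definition does not.

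Study Population requires participants to be "pregnant with gestational age 20 to 28 weeks at enrollment". Participant Allocation adds: "Participants will be randomized according to the randomization schedule based on when they complete the enrollment surveys".

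On analysis, the Data Analysis section states: "A shared random component generalized linear mixed model (GLMM) will be used to simultaneously describe and compare the effects". The outcomes covered are the clinical, behavioural and strengths outcomes across all measurement times. Time is a fixed effect. The time-by-group term is tested and removed if its P value is above .10. The covariates named are baseline nutrition, physical activity and sleep. Demographic or clinical characteristics that differ between groups at baseline may be considered as further covariates. Baseline weight is not named.

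The Objectives section hypothesises that "the PARITY program will improve maternal blood pressure, gestational weight gain, and cesarean birth rate in the intervention group", and says that the pilot will estimate the size of the effect relative to control.

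**The concern.** Three quantities of different kinds stand under one outcome label. Gain by 20 weeks is settled at or before allocation, by up to 8 weeks for someone enrolled at 28 weeks, so its expected group difference is zero. Gain at birth is gestational weight gain in the ordinary sense. Weight 6 weeks after birth is retention, because the pregnancy is over.

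Listing them together does little harm if each time is estimated separately. The difficulty comes from combining the list with the interaction rule. Once the time-by-group term is removed, the model reports one group effect common to all times, including the time at which no effect is possible. A stated purpose of the pilot is to supply effect sizes for a larger trial, and a common effect built this way would be biased toward zero as an estimate of the effect on gestational weight gain.

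**Working it through.** **1. Timing.** Enrolment is at 20 to 28 weeks (Study Population), and randomisation comes after the baseline surveys (Participant Allocation). A weight at 20 weeks is therefore at or before randomisation for everyone, and precedes it by up to 28 − 20 = 8 weeks. Whichever reference weight is meant, the 20-week entry cannot carry a program effect.

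**2. The plan's own figure.** The sample size section gives a detectable difference in blood pressure and gestational weight change of 0.81 SD with 25 per group, and 0.91 SD after 20% attrition (20 per group), at 80% power and two-sided alpha .05. I checked this with the noncentral t distribution, df = 2n − 2 and noncentrality d√(n/2):
- n = 25: 0.81 × √12.5 = 2.86, df 48, power 80.1%.
- n = 20: 0.91 × √10 = 2.88, df 38, power 80.1%.

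Both figures reproduce. They describe a single difference between two means, not an average over several times.

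**3. Dilution if the interaction is removed.** Assume a random-intercept model with complete data, under which the times carry equal weight. The article does not state the weighting. The common group effect is then (δ at 20 weeks + δ at birth + δ at 6 weeks)/3, with δ at 20 weeks = 0:
- Effect d at both later times: (0 + d + d)/3 = 2d/3. With d = 0.81 SD this is 0.54 SD.
- Effect d at birth, half of it at 6 weeks: (0 + d + d/2)/3 = d/2, or 0.405 SD.
- Effect d at birth only: (0 + d + 0)/3 = d/3, or 0.27 SD.

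If the 36-week time in the Outcomes section also applies to weight, there are four times. The fractions become 3/4 (effect at all three later times) and 1/4 (birth only).

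**4. How often the interaction would be removed.** Assume 25 per group, three times, SD 1 at each time, a common within-person correlation ρ of 0.5 or 0.8, and an F test on 2 and 96 df at the .10 level. The noncentrality is λ = (n/2) × Σ(δt − mean δ)²/(1 − ρ). For the pattern (0, d, d) the sum is (4/9 + 1/9 + 1/9)d² = 2d²/3, and (0, d, 0) gives the same sum. So λ = 12.5 × (2/3)d²/(1 − ρ) = 8.33d²/(1 − ρ).

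| True d (SD) | λ, ρ = 0.5 | removed | λ, ρ = 0.8 | removed | common effect, pattern (0, d, d) |
|---|---|---|---|---|---|
| 0.40 | 2.7 | 60% | 6.7 | 27% | 0.27 |
| 0.50 | 4.2 | 45% | 10.4 | 11% | 0.33 |
| 0.81 | 10.9 | 9% | 27.3 | 0.1% | 0.54 |

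For these two patterns, at the effect size used for planning, the term would usually be kept. The dilution matters mainly for moderate effects.

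**5. Pregnancy length.** The article gives no rate of gain. At an assumed 0.8 to 1.2 lb per week, a birth 4 weeks earlier means 3.2 to 4.8 lb less gain for that person. Between arms, a half-week difference in mean gestation would give only 0.4 to 0.6 lb. Gestational age at delivery is already collected as an exploratory outcome, so this can be examined.

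**The case against.** The definition can be read as a list of the times at which weight is taken from the record, not as a composite. The 20-week reading may be meant as the starting point: the abstract calls 20 to 28 weeks baseline, and the sample size section speaks of weight change. A separate analysis plan may say so. The interaction rule is also a general modelling choice that affects every repeated outcome, and without it the two-thirds and one-third figures vanish. Descriptive statistics at each time would still show the birth value separately.

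Much of this stands. Nothing says that the three values are summed, and the harm is conditional on the interaction being removed. But the outcome definition and the interaction rule are both fixed in this document. The definition lists 20 weeks among the outcome times, and no text makes weight a baseline covariate. The screening of characteristics that differ at baseline might bring it in, but does not ensure it.

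Four stronger readings are tempting and are not supported:
- **A built-in bias of several pounds from pregnancy length.** The figure is per person. A group bias of that size would need arms about 4 weeks apart in mean gestation, and the article hypothesises no effect on pregnancy length.
- **A firm contradiction over 36 weeks.** The Outcomes sentence is a collective summary that also covers delivery mode, which cannot be observed at 20 or 36 weeks. It is not a schedule for each outcome.
- **A result in either direction would be claimed as success.** The hypothesis speaks only of improving weight gain, and the Nutrition section's "These nutritional guidelines are consistent with healthy weight gain" describes content, not the endpoint. That is a missing detail which the full protocol or analysis plan may supply; two-sided testing is standard.
- **Gain per week is the only proper measure.** Total gain at birth is a legitimate endpoint, so the rate belongs in a sensitivity analysis.

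**Conclusion.** The point holds in a limited form. As written, the plan treats a value fixed at or before randomisation and a postpartum value as outcome times for gestational weight gain, and allows a model that estimates one group effect across them. If the interaction is removed and the three times are weighted equally, the reported effect is two thirds of the true one when it is present at both later times, and one third when it is present at birth only. If the interaction is kept, there is no such dilution. Under the assumptions in step 4, removal would occur in about 11% to 60% of trials for a true effect of 0.4 to 0.5 SD, and in at most about 9% at 0.81 SD.

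The power figures are correct and are not in dispute. This is a secondary outcome in a 60-person pilot, but its effect size is meant to inform a larger trial, so the change is worth making before analysis.

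**What to change.** - Remove the 20-week value from the repeated outcome. Use it, or the recorded weight nearest before randomisation where available, as a baseline covariate. For later enrollees these are different weights, so the plan should say which is used.
- Make weight gain at birth the gestational weight gain endpoint, and estimate the group difference at that time whatever the interaction P value.
- Add a sensitivity analysis that accounts for pregnancy length, for example gain per week, using the gestational age at delivery already collected.
- Report 6-week postpartum weight separately, as retention.
- Minor clarifications: state which direction or range counts as improvement, and align the time lists in Outcomes and Outcome Measures.

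The cost is wording, slightly more analysis work and one fewer repeated outcome time. The 20-week, birth and 6-week weights are already to be extracted. A weight closer to randomisation depends on what the record holds.
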